### Outcomes

The primary outcome is the change of hematoma volume 8 weeks after atorvastatin treatment on non-enhanced CT scan.

Secondary outcomes are changes of hematoma volume at the 4^th^, 12^th^, and 24^th^ weeks; MGS- GCS, GOS and ADL-BI scores; and improvements in neurological symptoms and signs and laboratory tests.

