**Discussion:**

Results of this trial will provide critical information regarding whether atorvastatin is an effective and safe alternative to surgical treatment of CSDH.

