## Background

Chronic subdural hematoma (CSDH) is a common type of encephalic hematoma with an incidence of 5/10,000 in the general population and 58/10,000 in people who are 70 years or older [1]. Head trauma is the most common risk factor for CSDH [2], along with age. CSDH occurs in up to 26.5 % of patients who are 65 years or older. Older patients also have a significantly higher recurrence rate as compared to the general population [3]. Incidences of CSDH and recurrent CSDH are expected to raise worldwide with an aging population. In addition, the increasing use of anticoagulant/antiplatelet therapies is also a common risk factor for CSDH in patients without a history of trauma [4] and poses a challenge for the surgical treatment of CSDH. Unlike subacute subdural hematoma (SSDH), spontaneous reabsorption is rare in CSDH and surgery has traditionally been the treatment of choice [5]. However, the rate of recurrent CSDH is high (approximately 25 %) in surgically treated patients [6], leading to a mortality of 11.1–13.5 % [7]. The surgical outcome is particularly poor for patients of 90 years or older [8].

Because of unsatisfactory outcomes of surgery, several adjuvant or conservative therapies have been clinically tested, including corticosteroids, as complementary therapies [1]. Dexamethasone is reported to effectively reduce the volume of CSDH after surgery [9–12]. It is also reported that perindopril (angiotensin converting enzyme inhibitor, ACEI) reduces the recrudescence of CSDH after surgery [13]. We have recently reported the effect of atorvastatin on reducing CSDH in 23 patients [14].

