### Treatment and intervention

*Atorvastatin:* oral intake of a 20 mg Atorvastatin tablet daily for 8 weeks.

*Placebo:* oral intake of a placebo tablet daily for 8 weeks.

At the end of the 8-week treatment, the volume of hematoma will be evaluated by CT scan for the following outcomes:A hematoma disappears or is significantly reduced from the size measured before the treatment. Regardless of whether a smaller hematoma remains, the patient will enter into the follow-up period and should not be continuously treated with atorvastatin.A hematoma does not change significantly or increases by CT scan at the end of 8 weeks of treatment (this can occur in patients who receive placebo). At the end of atorvastatin treatment, attending surgeons can decide if these patients need to receive surgery. The detailed medication and treatment during the process will be continuously recorded for 24 weeks.For any patients whose hematoma increases as determined by CT scan and/or neurological deficits progress during the follow-up period, he or she may undergo surgery. The detailed medication and treatments during the process will be recorded for 24 weeks.

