### Timeline schedule

Protocol-mandated assessments will be performed according to the schedule (Table 2). The study flow chart illustrates key steps of the trial (Fig. 1).

**Table 2 Tab2:** Visit and assessment schedule

Activities	Screening	Day 1	Days 2–6	Day 7	Week 2 ± 1D	Week 3 ± 1D	Week 4 ± 1D	Week 8 ± 3D (treatment end)	Week 12 ± 3D^4^	Week 24 ± 7D^4^
Informed consent	√									
History collection										
Inclusion/Exclusion	√									
Concomitant medication^1^		√	√	√	√	√	√	√	√	√
Physical examination	√			√	√	√	√	√	√	√
Surgery conversion		√	√	√	√	√	√	√	√	√
Efficiency observation										
Neurological symptoms^2^	√	√	√	√	√	√	√	√	√	√
Hematoma volume by CT^2^	√						√	√	√	√
MGS-GCS/ADL-BI^2^	√			√			√	√	√	√
GOS							√	√	√	√
Safety assessment										
Vital signs	√	√	√	√	√	√	√	√	√	√
Blood routine/Coagulation	√						√	√	√	√
Liver and renal function/Electrolyte/Lipids	√						√	√	√	√
Urinalysis	√							√		√
Electrocardiography	√							√		√
Pregnancy test	√									
Adverse events		√	√	√	√	√	√	√	√	√
Others										
Drug dispensing	√			√	√	√	√			
Drug recovery^3^				√	√	√	√	√		

*ADL-BI* Activities of Daily Life – the Barthel Index scale, *CT* computerized tomography, *D* day, *GOS* Glasgow Outcome Score, *MGS-GCS* Markwalder’s Grading Scale and Glasgow Coma Scale

^1^Records of combination therapy are required until the end of the trial

^2^Surgical therapy is considered in the case of deterioration in neurological symptoms and/or signs, MGS-GCS grading and increase of hematoma immediately imaging review then

^3^The remaining drugs need to be recovered

^4^At weeks 12 and 24, CT should be performed; other laboratory examinations will be selected when needed

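### Surgery, expected more often on placebo, distorts hematoma volume at weeks 12 and 24 whether operated patients stay in or are removed, and conversion to surgery is recorded but is not an outcome

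*Protocol article*

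**What the plan says.** All references are to the protocol article.

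- **Outcomes.** The primary outcome is the change in hematoma volume at week 8. The section continues "Secondary outcomes are changes of hematoma volume at the" 4th, 12th and 24th weeks, then lists the functional scores, symptoms and signs, and laboratory tests. The Abstract and the Study objective section also name volume at weeks 12 and 24. None of the three lists surgery.
- **Treatment and intervention.** If the hematoma is unchanged or larger at week 8, "attending surgeons can decide if these patients need to receive surgery". The section remarks of such non-response that "this can occur in patients who receive placebo". If the hematoma grows or deficits progress during follow-up, "he or she may undergo surgery". In both cases medication and treatment are recorded to week 24.
- **Methodology.** Patients whose neurological symptoms worsen during the trial get an emergency scan and any necessary surgery, and are then taken out of the trial.
- **Timeline schedule, Table 2.** The row "Surgery conversion" is ticked in every column from Day 1 to Week 24, that is, in all columns after Screening. CT is scheduled at weeks 4, 8, 12 and 24.
- **Purpose.** The Abstract says the results will show "whether atorvastatin is an effective and safe alternative to surgical treatment of CSDH". The Study objective section frames the primary objective as shrinking or clearing the hematoma at two months without an operation.

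**The concern.** Surgery evacuates the hematoma, so it acts directly on the quantity measured at weeks 12 and 24. It is offered to treatment failures, and the protocol expects more of these on placebo. An operated failure whose later scan is used looks like a success. An operated failure who is removed leaves behind a group enriched for responders. Both mechanisms work harder in the placebo arm and pull the arms together.

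The event that creates the problem is also the one closest to the trial's stated purpose. If the drug spares patients an operation, the conversion rate shows it most directly. The data are scheduled for collection, yet the result has no pre-specified place among the outcomes. A real benefit could appear as a modest late difference in volume, with the difference in operations reported only incidentally.

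**Working it through.** The protocol gives no figure for how often surgery will occur and no standard deviation for volume, so there is no figure of its own to reproduce on this point. Its sample size is not an input. What follows uses a response proportion as a stand-in for volume change.

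**Inputs**
- Response 80% on atorvastatin and 50% on placebo (Sample size section, read as proportions of patients responding). Non-response is therefore 20% and 50%, and the starting difference is 80 − 50 = 30 points.
- f, the share of non-responders operated on, is not in the document. Assumed values are 25%, 50% and 75%, the same in both arms.
- Patients not operated on are assumed to keep their week-8 status.

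**Reading A: operated patients stay in, their scans count, and surgery always clears the hematoma**

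Apparent response is p + (1 − p)f, so the difference is 0.30 × (1 − f).

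**Reading B: operated patients are removed**

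Apparent response among those left is p / [1 − (1 − p)f].

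| f | A: arms | A: difference | B: arms | B: difference | Converted to surgery |
|---|---|---|---|---|---|
| 25% | 85.0% vs 62.5% | 22.5 | 0.8/0.95 = 84.2% vs 0.5/0.875 = 57.1% | 27.1 | 5% vs 12.5% |
| 50% | 90.0% vs 75.0% | 15.0 | 0.8/0.90 = 88.9% vs 0.5/0.75 = 66.7% | 22.2 | 10% vs 25% |
| 75% | 95.0% vs 87.5% | 7.5 | 0.8/0.85 = 94.1% vs 0.5/0.625 = 80.0% | 14.1 | 15% vs 37.5% |

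The last column is 0.20f versus 0.50f.

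**Softer version of A.** The Background section says "the rate of recurrent CSDH is high (approximately" 25%) after surgery. If a quarter of operations fail to hold, the difference is 0.30 × (1 − 0.75f), which gives 24.4, 18.8 and 13.1 points.

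**Low surgery share.** At f = 10%, reading A gives 0.30 × 0.90 = 27.0 points. Reading B gives 0.8/0.98 − 0.5/0.95 = 81.6% − 52.6% = 29.0 points. The effect is then minor.

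**Operated patients kept as failures.** The arms stay at 80% and 50%, and the 30 points are preserved at every f.

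**The two sections on operated patients.** They overlap for a patient whose deficits progress during follow-up and who is operated on. Under Treatment and intervention, recording continues to week 24. Under Methodology, the patient leaves the trial. So the document does not settle whether week-12 and week-24 scans will exist for that patient.

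**The case against.** The strongest reply is that the protocol never says how volume is tested. The Data analysis section names ANCOVA only for the Markwalder/Glasgow and Barthel scores. A rule for scans after surgery is commonly left to the analysis plan, which is not shown. This stands. A reader might infer that the plan compares later volumes as though no one had been operated on, but the document does not say so.

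A second reply is that the illustration rests on an assumed surgery share and a responder proxy for a continuous outcome. Surgery is discretionary, and patients enter without an immediate need for it, so the share could be low. This also stands, and it is why the low-share case is shown. A reader might go on to infer a loss of planned power. The protocol states no power for any secondary outcome, so none can be said to be lost.

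Third, the affected time points are secondary, and the bias runs toward no difference, so a false claim of benefit is not the risk. That is fair and limits the severity.

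It might also be said that removal, as in the Methodology section, already deals with the problem. It does not: removal shrinks the difference too, only less. Nor can an analysis plan settle by itself whether operated patients are followed, or easily add an outcome that the protocol omits from all three of its lists.

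**Conclusion.** The point holds in a limited form. Volume at weeks 12 and 24 is exposed to surgery that is expected more often on placebo. Both ways of treating operated patients that the document suggests bias the comparison toward no difference. Under the stated assumptions, the 30-point difference falls to between 22.5 and 7.5 points if scans are counted, or between 27.1 and 14.1 points if operated patients are removed, for 25% to 75% of non-responders operated on. It barely moves if few are operated on. These figures show direction and scale and do not predict the volume result.

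Two facts need no assumption: conversion to surgery is scheduled for capture but is not an outcome, and the two sections disagree on whether some operated patients remain in the trial. The change is worth making, but the week-8 primary outcome is not the target of this point.

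**What to change.** 1. List conversion to surgery, by week 8 and by week 24 and in all randomised patients, as a secondary outcome in the Abstract, the Study objective section and the Outcomes section.
2. Reconcile the Treatment and intervention and Methodology sections on whether operated patients stay in follow-up. This concerns data collection only. It changes no decision to operate, and no view is taken here on when surgery should be done.
3. State that operated patients stay in the week-12 and week-24 volume comparisons as treatment failures, for example by giving them the worst rank. Show observed post-operative volumes as supportive results. The worst-rank approach needs only the fact of surgery, so it works even where no later scan exists.

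The cost is wording and a little analysis, because Table 2 already schedules the data. The downside is small: the later volume result becomes partly composite, mixing volume with having been operated on, and should be described that way.

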### Sample size

We have previous shown, in a pilot study of a small patient cohort, that a significant reduction in hematoma volume was found in 95.7 % of CSDH patients treated with atorvastatin. This result provides a base for the power calculation of this trial where we assume that 80 % of patients in the treatment group achieve reduction in hematoma volume and neurological deficits as compared to 50 % reduction in placebo control patients. When the test power (1 − β) is 80 %, we will need to recruit 52 patients in each treatment group based on a 2-size data comparison to reach statistical significance. When a 20 % drop-out rate is taken into the consideration, the sample size is expanded to 126 patients. However, we propose to recruit 200 patients, with 50 % randomly assigned to the atorvastatin treatment group, to meet the requirement of the CFDA for drug registration that the number of cases in treatment group shall not be less than 100 in a phase II clinical trial.

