### Methodology

The ATOCH study is designed based on our previous experience in treating CSDH with atorvastatin, showing that 22 out of 23 patients achieved complete hematoma elimination during the follow-up period after atorvastatin treatment. We, therefore, expect a significant volume reduction in the hematomas of patients on atorvastatin. However, since this is a conservative treatment trial of a clinical condition that is traditionally treated surgically, we limit our recruitment to patients who have a small-medium volume of CSDH and whose MGS-GCS is less than 3. To reduce adverse risks, especially patients on placebo, all patients will be closely monitored for acute neurological deterioration. If neurological symptoms deteriorate during the trial, patients will receive an emergency head CT scanning and necessary surgery. Such patients will be removed from the trial.

Except for rhabdomyolysis and impact on liver function, atorvastatin is considered to be generally very safe. Thus, we do not plan to waive SAE for this trial protocol. If a patient develops any suspected related side effects, he or she will be immediately excluded. If atorvastatin-related side effects are confirmed, treatment will be terminated and affected patients will be followed for 6 months.

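### The stated power is for a responder rate that is not a listed outcome, so power for the primary outcome (week-8 change in hematoma volume) is not demonstrated; the responder figure is also mislabelled, since 52 per arm is the 90% power result

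*Protocol article*

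**What the plan says.** The Outcomes section of the protocol article defines the primary endpoint: "The primary outcome is the change of hematoma volume 8 weeks after atorvastatin treatment on non-enhanced CT scan". The Abstract places this at the end of the 8-week treatment. Neither gives a responder cut-off. The secondary outcomes are volume changes at other weeks, then the MGS-"GCS, GOS and ADL-BI scores; and improvements in neurological symptoms and signs and laboratory tests". No proportion of responders is listed.

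The Sample size section starts from a pilot in which "a significant reduction in hematoma volume was found in" nearly all treated patients (95.7%), and rests the calculation on that result. The effect assumed for the active arm is a share of 80%, described by the words "of patients in the treatment group achieve reduction in hematoma volume and neurological deficits as compared to"; the control figure is 50%. From these two rates it gives 80% power, 52 per arm, and 126 in total after 20% drop-out. It then sets recruitment at 200, because the regulator requires at least 100 treated patients in a phase II trial.

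The Methodology section describes what appears to be the same pilot as "22 out of 23 patients achieved complete hematoma elimination during the follow-up period after atorvastatin treatment".

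**The concern.** The quantity that is powered differs from the primary endpoint in two ways. It is binary where the primary is a quantitative change, and it joins volume with neurological deficit where the primary is volume alone. The Treatment and intervention section does sort week-8 scans by whether the hematoma is gone or clearly smaller. That sorting guides management, has no numerical cut-off, leaves out neurology and is not named as an outcome, so it cannot serve as the missing responder definition.

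At stake is how the primary result will be read. Because 200 comes from a regulatory floor, nothing in the article says what difference in volume the trial can detect. If the volume comparison were null, a reader would be inclined to set it against the 80% figure, which belongs to another test. That figure does not match its own inputs either.

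**Working it through.** **Inputs.** Rates of 80% and 50%, power 80%, 52 per arm, 20% drop-out, 126 and 200 in total (Sample size); two-sided test at 0.05 (Data analysis); 1:1 allocation (Trial design). The placebo figure is worded as a 50% reduction and is read here as 50% of patients.

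**Step 1: the plan's own figure.** Pooled two-proportion formula, per arm, with mean rate p = 0.65:

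n = [z(α/2)·√(2p(1−p)) + z(β)·√(p1(1−p1) + p2(1−p2))]² / (p1 − p2)²

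- √(2 × 0.65 × 0.35) = √0.455; √(0.8 × 0.2 + 0.5 × 0.5) = √0.41; (0.8 − 0.5)² = 0.09.
- 80% power: (1.960 × √0.455 + 0.842 × √0.41)² / 0.09 = (1.322 + 0.539)² / 0.09 = 38.5, so **39 per arm**.
- 90% power: (1.322 + 1.282 × √0.41)² / 0.09 = (1.322 + 0.821)² / 0.09 = 51.01, so **52 per arm**.

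Other versions at 80% power, two-sided, do not give 52: 45 with continuity correction, 36 unpooled, 38 by arcsine, 44 by Fisher's exact test. Solving the pooled formula for power at n = 52 gives 90.6%. So 52 is exactly the 90% power result, which also confirms that the calculation compares two proportions.

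The 126 follows as 52 × 1.2 = 62.4, rounded to 63, times 2. (Dividing by 0.8 would give 65 per arm, 130 in total; with 200 planned this has no effect.)

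**Step 2: the primary endpoint.** The article gives no mean difference or SD for volume change, so its power cannot be computed from the document. What can be stated is the standardised difference d = (mean difference)/SD that is detectable with 80% power, for an unadjusted two-sample t-test at two-sided 0.05 (noncentral t):

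- 52 per arm: d = 0.555
- 80 per arm (100 × 0.8): d = 0.446
- 100 per arm: d = 0.398

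Power over a range of **assumed** d:

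| d | 52 per arm | 80 per arm | 100 per arm |
|---|---|---|---|
| 0.2 | 17% | 24% | 29% |
| 0.3 | 33% | 47% | 56% |
| 0.4 | 52% | 71% | 80% |
| 0.5 | 71% | 88% | 94% |
| 0.6 | 86% | 97% | 99% |
| 0.8 | 98% | >99% | >99% |

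The stated 80% carries over to none of these columns without an assumption about d that the article does not make.

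**Step 3: the pilot basis.** 22/23 = 95.65%, so both sections appear to report one result, once as significant reduction and once as complete elimination during follow-up. Neither is a week-8 response in volume and neurology jointly. As described, the pilot reports only treated patients, so it gives no placebo rate.

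**The case against.** The strongest reply is that nothing here shows a power shortfall. That stands. If the 80% and 50% came from cutting a normally distributed volume change with common SD at one threshold, ignoring the neurological component, the implied difference would be z(0.80) − z(0.50) = 0.84 SD. Power would then be about 99% even with 52 per arm. Adjustment for baseline volume, of the kind that the Data analysis section plans for MGS-GCS and ADL-BI, would usually raise power further. A reader might infer from the mismatch that the trial is underpowered, or that its primary analysis has less than the stated 80%. Without an SD or a mean difference, the document supports neither inference.

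Second, the sample size does not depend on this calculation: 200 is set by the regulatory minimum, and no power is claimed for 200. This also stands. It limits the consequence to the power statement and its use in interpretation.

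Third, the two pilot descriptions need not conflict. A hematoma that is eliminated has also been reduced, and the time points may differ. A reader might take them as a contradiction, but they show only inconsistent wording, and the assumed 80% is well below 95.7%. This part is secondary.

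What the reply does not remove is that the article presents a power figure for a quantity it does not list as an outcome, and that this figure disagrees with its own inputs.

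**Conclusion.** The point holds in a limited form. Power for the week-8 change in hematoma volume is undemonstrated, not shown to be too low, and there is no case for a different N. At the planned size the trial has 80% power for about 0.45 SD after 20% loss, or about 0.40 SD without loss. This rests on an unadjusted t-test, equal arms and the plan's two-sided 0.05. Whether 0.45 SD is a realistic or worthwhile difference cannot be judged from the article.

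The mislabelling is firm. Under the stated rates and significance level, 80% power needs 39 per arm (45 with continuity correction), and 52 per arm corresponds to 90.6%. This error makes the stated power too low for the responder test, so it is conservative there, but it says nothing about volume.

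Severity: should be fixed. The correction changes what the trial can claim about its primary result, not its size or conduct.

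**What to change.** Keep N at 200 and revise the Sample size section as follows.

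1. State power for the primary outcome. For example: with 200 randomised and 20% loss (80 per arm), the trial has 80% power at two-sided 0.05 to detect a difference of about 0.45 SD in week-8 volume change by an unadjusted two-sample t-test (about 0.40 SD with 100 per arm).
2. Translate this into mL with a stated assumed SD. A blinded pooled SD is an alternative, but only from enrolled patients who already have a week-8 CT. The Trial status section reports 96 enrolled and does not say how many have reached that visit. If trial data are used, say that this is a blinded variance estimate without comparison of the arms, since the article rules out an interim analysis, and note that a pooled SD includes any difference between the arms.
3. If the responder calculation is kept, label it supportive and correct it: either 90% power with 52 per arm, or 39 per arm with 80% power.
4. Describe the 22/23 pilot result in the same way in the Sample size and Methodology sections.

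Cost: wording only if an assumed SD is used; a small blinded data extract otherwise. The stated figure may become less favourable than the present one.

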### Data analysis

A 2-tailed test will be performed and a *p* value of less than or equal to 0.05 is considered to be statistically significant. Statistical analysis will be performed by SAS 9.3 (SAS Institute Inc., Cary, NC, USA). The quantitative parameters include group means, standard deviation, median, minimum value and maximum value. A secondary descriptive analysis will summarize improvements of neurological symptoms. For the secondary outcome measures, neurological symptoms and clinical signs of patients in each group are first to be described. Both MGS-GCS and ADL-BI as measured at admission, 3 and 6 months are statistically compared using analysis of covariance (ANCOVA) with the treatment group as a fixed effect and using MGS-GCS and ADL-BI baseline values as covariates.

